#### Plans to give access to the full protocol, participant-level data, and statistical code

This paper provides the full protocol. Interested individuals should contact the study co-Chief Investigator (EP) if interested in other data or documentation of the study.

### Oversight and monitoring

#### Composition of the coordinating centre and trial steering committee

A programme management group comprising the co-Chief Investigators, co-applicants, the programme manager, the trial coordinator, the statistician and researchers from each of the research sites who will meet quarterly to oversee the general running of the project and all its components such as the progress of the trial and review recruitment. The trial will be managed on a day-to-day basis by the Programme Manager supported by the Chief Investigators and Sheffield CTRU team. The group will provide timely reports on the progress, or completion, termination or discontinuation of the study to the ethics committees.

The trial will be overseen by an independent Programme Steering Committee (PSC) consisting of the Chief Investigators of the study, an independent chair and at least two other independent members (including someone with lived experience). The PSC will meet on at least a six-monthly basis via face-to-face meetings or an online platform to discuss progress of the trial, or more often as appropriate. The Data Monitoring and Ethics Committee (DMEC), research team and statisticians will report to the PSC as necessary.

#### Composition of the data monitoring committee, its role, and reporting structure

The committee will consist of independent experts, including a statistician and mental health professionals, who are independent of the principal investigator and the study team. Its remit will be to monitor the trial data, in particular quality control and quality assurance of the data collected, and progress of the trial including adherence to the trial protocol. The committee will also examine and ensure that the dignity, rights, safety and wellbeing of all study participants are maintained at all stages of the trial. Data reports will be supplied, including any adverse events, and the committee will have access to summary data and documentation. The Chair of the DMEC will be informed of any adverse events that arise from the study or regarding participants during the study period, and they will be in a position to recommend suspension or ending the trial depending on the severity of the adverse event.

#### Adverse event reporting and harms

Data on adverse events will be collected on a case-by-case basis. All adverse events and serious adverse events will be evaluated by an independent reviewer and the Chief Investigator within 24 h of the event being reported. A summary table of adverse events will be compiled on an ongoing basis and will be provided to the DMEC at DMEC meetings. The summary will include a description of the adverse event, the date of onset, severity, action taken, outcome, whether the adverse event was expected or not, and an evaluation of the relationship of the adverse event to study procedures. Adverse event reports and summaries will not include any patient identifiable data and participants will be identified only by study ID number. Example adverse events include, but are not limited to:Muscle soreness which fails to resolve 72 h following a physical activity sessionSubstantial increases in pre-existing pain which fails to resolve 72 h following a physical activity sessionDevelopment of new musculoskeletal pain which fails to resolve 72 h following a physical activity sessionInjuries sustained as a result of an accident incurred travelling to or from a physical activity session

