#### Intervention description

The SPACES intervention aims to support people with SMI to initiate and maintain physical activity. The intervention comprises two core components, an 18-week group-based physical activity component and a one-to-one consultation component, both of which are facilitated by a physical activity coordinator (PAC: NHS staff with suitable experience to deliver the intervention). Suitable PAC experience will include previous history of delivering physical activity interventions to those with SMI and relevant physical activity delivery training and qualifications. The intervention will last up to 20 weeks (one-to-one consultations are offered prior to the physical activity component), with participants being offered up to 18 group physical activity sessions, up to 10 one-to-one sessions consisting of 3–6 long form consultations (30–60 min) and 2–4 check-ins (15–30 min). The intervention group will include between 6–12 participants and be supported by two PACs (four to six are trained at each NHS site for programme continuity e.g., covering annual leave). All PACs will receive training and a PAC manual on how to deliver the intervention to aid consistency. PACs will also receive ongoing bi-weekly support from the SPACES central team during the intervention delivery.

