**Physical Activity**						
Accelerometer data collection	10 days	X			X	X
Adverse event reporting		Ongoing collection				

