### Secondary efficacy outcome measures

Secondary outcome measures include body mass index (weight (kg) / [height (m)]^2^), depression (PHQ-9; [24]), anxiety (GAD-7; [25]), physical activity and sedentary behaviours (accelerometer-assessed metrics & SIMPAQ; [26]), health-related quality of life (EQ5D [27], SF-12 [28], REQoL [29]), healthcare resource ​​use collected via a bespoke questionnaire designed for SPACES (see Table 1), and adverse events.

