We will also include, as part of the feasibility analysis, estimation of the effect size for accelerometer-determined physical activity 6-months post-randomisation (the probable primary endpoint for the definitive study), defined as the mean (averaged over all available valid days) minutes of MVPA per day, with confidence interval estimates to check that the likely effect is within a clinically relevant range (as confirmation that it is worth progressing with the full trial (i.e. 95% CI includes a difference of 6 min of MVPA per day)). For this we will use a partially clustered mixed effects model with 6-month minutes of MVPA as the outcome and baseline minutes of MVPA, site and randomised group as fixed effects and SPACES intervention groups as random effects. The ICC from this model will be reported and will inform the ICC estimate for the main trial. This information along with the acceptability of the study design and protocol to patients/GPs; the safety of the intervention; adherence to the intervention, patient recruitment and attrition/retention rates will enable us to determine whether or not the definitive RCT is feasible, within a satisfactory timescale and cost envelope using UK sites alone.

We will estimate the intervention costs based on the delivery of the related activities and the study records over the intervention period. We will also test the feasibility and acceptability of the bespoke health care and service use questionnaire. Analysis of the completeness of participants’ responses and use of listed services together with additional services recorded by participants, will enable further revision to collect most relevant data in the full RCT and eliminate questions with few responses. The completeness and descriptive statistics of healthcare resources and EQ-5D-5L will be summarised by participants’ allocated study arm. No formal cost-effectiveness analysis will be undertaken as the feasibility study is not sufficiently powered.

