#### Methods for additional analyses (e.g., subgroup analyses)

Qualitative data will be analysed utilising an inductive approach and thematic analysis [40] to explore both participants and intervention delivery team experiences of the SPACES intervention. Participant data will be categorised to understand different perspectives. Qualitative analysis software, NVivo, will be used to process and analyse the data. Feedback from both participants and PACs will inform refinement of the intervention, including the intervention manual and training, with the aim to improve the acceptability and feasibility of the SPACES intervention.

Critical variables to enable success in the full RCT (workstream 3) will follow a traffic light system with recruitment of 100%, i.e., an average of 2 participants per centre per month being green, 50–99% (1 – 1.9 participants per month) being amber, and below 50% being red. This will enable us to select the correct number of centres for the full RCT. We will also test our ability to achieve follow-up at our target rate in the feasibility study, and to ensure there is equal retention between arms.

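### Adverse events are collected case by case from arms with very unequal staff contact, so counts by arm are open to detection bias

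*Protocol article*

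**What the plan says.** The section on adverse event reporting and harms states: "Data on adverse events will be collected on a case-by-case basis". It gives four examples, described as non-exhaustive. Three concern soreness or pain persisting after a physical activity session, and the fourth concerns injury on the journey to or from one. The running summary for the data monitoring committee covers severity, expectedness and relationship to study procedures. No tabulation by arm is mentioned.

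In Table 1 the adverse event row reads "Ongoing collection". The other outcomes followed up in both arms are marked at 3 and 6 months.

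The secondary outcome list ends with "healthcare resource ​​use collected via a bespoke questionnaire designed for SPACES (see Table 1), and adverse events", with no restriction to one arm. The section on the choice of comparators says that the usual care arm is there so that differences in the study outcomes can be understood.

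On progression, the statistical methods section says that "the safety of the intervention; adherence to the intervention, patient recruitment and attrition/retention rates will enable us to determine whether or not" the definitive trial is feasible. The progression criteria with numbers lie elsewhere: the MVPA interval ("95% CI includes a difference of 6 min of MVPA per day") and the recruitment traffic light ("recruitment of 100%, i.e., an average of 2 participants per centre per month being green").

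On contact, the intervention description has "participants being offered up to 18 group physical activity sessions, up to 10 one-to-one sessions", and the adherence section adds a call after two consecutive missed sessions. The blinding section says that participants, clinicians and researchers cannot be blinded.

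**The concern.** An event is counted only if it occurs and someone on the trial hears of it. Intervention participants are in front of trial staff most weeks for about four months, and those staff are alert to exercise-related complaints. Usual care participants have two scheduled assessments after baseline, and the article schedules no adverse event question at either. The examples steer reporters towards events that only the intervention arm can have.

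If true risk were equal, the intervention arm would still be expected to show more recorded events. Relatedness assessment helps only in part. In a population with high background morbidity, judging whether a new pain, injury or relapse is due to the programme is hard without a background rate collected in the same way. At stake are how the secondary safety outcome is read by arm and, through it, the safety input to the full-trial decision.

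**Working it through.** The article gives no adverse event rate, safety threshold or safety sample size, so there is no figure to reproduce. Two checks are possible.

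**1. Scheduled contacts after randomisation**

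The inputs come from the intervention description (up to 18 group sessions, 3–6 long consultations, 2–4 check-ins) and the data collection section (follow-up at 3 and 6 months).

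- Extra contacts offered to the intervention arm: 18 + 3 + 2 = 23 to 18 + 6 + 4 = 28.
- Adding the two shared follow-ups: 25 to 30, against 2 in usual care.
- Ratio: 25/2 = 12.5 to 30/2 = 15, if everything offered is taken up.

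**2. Illustration of the possible artefact (risks and detection probabilities are assumed)**

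Let p be the true risk, equal in both arms, and s_I and s_C the probabilities that an event is recorded in the intervention and usual care arms.

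- Observed risks: o_I = p·s_I and o_C = p·s_C.
- Spurious difference = p(s_I − s_C).
- Spurious risk ratio = s_I/s_C, whatever p is.
- 95% half-width for the difference = 1.96·√[o_I(1 − o_I)/n + o_C(1 − o_C)/n].

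The sample size section expects 48 to 140 participants. With 1:1 allocation, n is 24 to 70 per arm.

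Worked case: p = 0.20, s_I = 0.90, s_C = 0.50. Then o_I = 0.18, o_C = 0.10, the difference is 0.08 and the ratio 1.8. With n = 24 the half-width is 1.96·√[(0.1476 + 0.0900)/24] = 0.195.

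| True risk | Detection, intervention / usual care | Observed | Spurious difference | Half-width, n = 24 | Half-width, n = 70 |
|---|---|---|---|---|---|
| 10% | 90% / 70% | 9% / 7% | 2 points | 15.3 | 9.0 |
| 10% | 90% / 50% | 9% / 5% | 4 | 14.4 | 8.4 |
| 10% | 90% / 30% | 9% / 3% | 6 | 13.3 | 7.8 |
| 20% | 90% / 70% | 18% / 14% | 4 | 20.7 | 12.1 |
| 20% | 90% / 50% | 18% / 10% | 8 | 19.5 | 11.4 |
| 20% | 90% / 30% | 18% / 6% | 12 | 18.1 | 10.6 |
| 40% | 90% / 70% | 36% / 28% | 8 | 26.3 | 15.4 |
| 40% | 90% / 50% | 36% / 20% | 16 | 25.0 | 14.6 |
| 40% | 90% / 30% | 36% / 12% | 24 | 23.2 | 13.6 |

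The risk ratios are 1.29, 1.8 and 3.0 for usual care detection of 70%, 50% and 30%. The spurious difference is smaller than the half-width in 8 of 9 cases at 24 per arm and in 6 of 9 at 70 per arm. With equal detection (90% in both arms) the expected difference is 0 and the ratio 1.0.

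**The case against.** A reader might infer that a biased between-arm safety comparison decides whether the full trial goes ahead. The article does not support that. It names only the safety of the intervention, as one of several inputs, with no contrast and no threshold. That input can be judged from intervention-arm events and their relatedness. The measures listed for summary by randomised group do not include adverse events, although this is weak evidence because the list also omits the GAD-7.

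Other objections carry weight:

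- The case-by-case wording may describe how each report is handled, not how events are elicited. Purely spontaneous collection is therefore an inference. The data collection section says that secondary outcomes are gathered at 3 and 6 months, which could be read to include adverse events, and the wording of the forms need not appear in an article.
- Usual care events do not all go unrecorded. Table 1 collects mental-health admissions, referrals, medications and healthcare resource use in both arms at 3 and 6 months. These recover some serious events, but not specifically falls, injuries or persistent pain.
- Setting 30 contacts against 2 compares a ceiling with a floor. Attendance is voluntary, and both arms also have accelerometer handovers and regular communication.
- The examples are expressly not a complete list.
- The analysis is descriptive, without formal testing.

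These points limit the strength of the finding but do not remove it. The stated method is case-by-case and ongoing, Table 1 does not place adverse events at the shared visits, contact is clearly unequal, and nobody who reports or records events is masked.

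**Conclusion.** The point holds as a risk to interpretation, with modest consequences. Adverse event counts by arm would not be comparable as collection is described, and the likely direction is to overstate harm in the intervention arm. Neither direction nor size can be established from the document. The range of 2 to 24 points rests on assumed true risks of 10% to 40% and assumed detection of 90% against 30% to 70%. At the planned size such a difference would often lie within sampling error, but it is systematic and a larger sample would not remove it. It would be wrong to conclude that the progression decision itself is biased, because the article does not tie that decision to a contrast between arms.

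**What to change.** Follow-up closed on 18 December 2023, so no question can be added to this trial. Its report can still do four things:

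1. Give session-linked events as an intervention-arm rate per session attended. The participant logs supply the denominator. List other spontaneously reported events separately.
2. State that raw spontaneous counts are not comparable between arms.
3. Use the mental-health admissions and resource-use data, collected on the same schedule in both arms, for any contrast.
4. Say whether the safety input to progression was intervention-arm experience or a comparison of arms.

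For the full trial, put the same short structured adverse event question to both arms at the 3- and 6-month assessments (for example on injury, falls, new or persistent pain, and unplanned hospital attendance). Mark it at those visits in the schedule, and base any by-arm comparison on those answers alone.

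The cost is one short item on existing forms, a reporting line and a few more events to process. It will not remove all bias, because unblinded participants and researchers may still report or record differently by arm.

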### Frequency and plans for auditing trial conduct

To review study conduct, meetings with the independent programme steering committee will be held six monthly. In addition, programme management team meetings will be held monthly with key stakeholders.

### Plans for communicating important protocol amendments to relevant parties (e.g., trial participants, ethical committees)

Protocol changes that impact study procedures or risk to human subjects will be approved by the West of Scotland NHS Research Ethics Committee and if applicable reflected in a revised participant information sheet and consent form which will be reviewed and signed by all active participants. Protocol changes will also be reported to NIHR PGfAR in progress reports.

#### Dissemination plans

Findings from this study will be shared publicly and disseminated through publication in peer-reviewed journals, conference presentations and social media outlets.

## Discussion

This protocol outlines the methods to be used in the SPACES feasibility and acceptability trial. This study outlines step two (assessment of intervention feasibility and evaluation design) or four, of the NIHR’s updated framework on developing complex interventions and considers the six core elements for intervention design [41]. We know that people living with SMI, on average, die 15–20 years prematurely [1], with over 70% of these deaths being attributable to preventable physical health conditions [2] linked to health behaviours such as physical (in) activity and sedentary behaviour. Furthermore, research demonstrates that people with SMI are less active than the general population [3, 7] and experience unique barriers to being physically active [8]. This study, therefore, aims to address an important health need, with an opportunity to manifest positive strategies to reduce the widening health inequality gap between those with SMI and the general population. Conventional treatment methods to reduce this gap have not necessarily been successful in improving physical health or QoL [9] for those with SMI. Previous studies attempting to address physical activity behaviour for the SMI population have had various limitations, such as sample size, however, have demonstrated promise for behaviour change [17]. In addition, the feasibility and acceptability of a physical activity intervention delivered within NHS pathways is yet to be understood.

Through assessing the feasible and acceptable of the SPACES intervention, we will uncover the necessary information to improve and refine the intervention and implementation process. This knowledge will be used to inform a larger scale RCT, investigating the effectiveness of the SPACES intervention for various health outcomes. Understanding effective methods to enable people with SMI to live healthier, more active lives, is likely to have a positive impact on the widening health inequalities gap between those with SMI and those without SMI. The SPACES intervention was co-produced by those with lived experiences of SMI and professionals who support those with SMI, thus, is well-positioned to reveal potentially effective strategies to support those with SMI to live physically active lives.

## Trial status

Trial recruitment commenced on 01st December 2022 and was completed by 20th April 2023. The trial closed with all follow-ups complete on the 18th December 2023. Current protocol version is 1.2 (dated 12/02/2024). 

## Data Availability

Any data required to support the protocol will be supplied on request.

## Abbreviations

AIM: Acceptability Intervention Measure
BMI: Body Mass Index
CI: Confidence Interval
CMHT: Community Mental Health Team
CONSORT: Consolidated Standards of Reporting Trials
CTC: Consent to Contact
CTRU: Clinical Trials Research Unit
DMEC: Data Monitoring and Ethics Committee
DSM-V: Diagnostic and Statistical Manual of Mental Disorders – 5
EQ5D: Euro Quality of Life 5 Dimensions
GAD: Generalised Anxiety Disorder assessment
GP: General Practitioner
Hz: Hertz
ICD: International Classification of Diseases
ISRCTN: International Standard Randomised Controlled Trial Number
MVPA: Moderate to Vigorous Physical Activity
NIHR: National Institute for Health and Care Research
NHS: National Health Service
PA: Physical Activity
PAC: Physical Activity Coordinator
PGfAR: Programme Grants for Applied Research
PHQ: Patient Health Questionnaire
PSC: Programme Steering Committee
QoL: Quality of Life
RCT: Randomised Controlled Trial
ReQol: Recovering Quality of Life
RPE: Rate of Perceived Exertion
SF-12: Short Form-12
SIMPAQ: Simple Physical Activity Questionnaire
SMI: Severe Mental Ill Health
SOP: Standard Operating Procedure
UK: United Kingdom
